### Safety and privacy

Due to the nature of the intervention, serious AEs are unlikely to occur, and we consider the intervention low risk. A data safety and monitoring board is not installed.

Some precautions are taken to optimise participant safety. First, regardless of their study allocation, participants will be referred to their GP or treating physician if deemed necessary based on their baseline or outcome parameters and local guidelines. Second, AEs will be monitored through three 6 monthly questionnaires, for which participants will receive notifications on their smartphone and reminders through email (UK) or SMS (China). If the participant is not able to fill in the questionnaire, an informant can be contacted. A blinded researcher will, with explicit permission gained through the informed consent procedure, cross-check all reported AEs by consulting the participant’s GP or treating physician. Third, the PRODEMOS platform is built in accordance with the highest security requirements in healthcare. It complies with NEN 7510, the Health Insurance Portability and Accountability Act, ISO 133485 and General Data Protection Regulation.

### Protocol adjustments due to COVID-19 pandemic

As a result of the COVID-19 pandemic and related local research restrictions, certain adjustments have been made to the original study protocol as published on the International Standard Randomised Controlled Trial Number Register (ISRCTN). First, recruitment was planned to start in early 2020 but had to be suspended until January 2021. Second, as it is difficult to predict the development of the pandemic and associated restrictions, we have slightly amended the study protocol to allow for flexible measurement procedures at baseline that can be operationalised in either one or two face-to-face visits and for a flexible intervention duration of 12–18 months. However, we will strive for a follow-up period of 18 months in as many participants as possible.

### Patient and public involvement

We have received valuable input into the design of the study and mHealth platform from multiple interactive sessions with GPs, health coaches, researchers, representatives of people living with dementia, community leaders and policy makers. Needs and views regarding the intervention were assessed through interviews and focus groups with potential end users in both countries. All patient-facing material used in the UK has been reviewed by potential end users. Qualitative evaluations of the pilot study with research staff, coaches and patient participants were used to refine the intervention and study procedures.

### Statistical analysis

#### Sample size

The CAIDE Score will be used as primary effectiveness outcome. We decided to use a difference of 0.186 points on the CAIDE Score between the average of both study groups as a minimum target threshold, because this difference was observed in the Prevention of Dementia by Intensive Vascular Care trial after 2 years (p=0.005; intervention group=−0.290±1.47 SD and control group=−0.104±1.36 SD). Attrition after 2 years of follow-up was 21% in this study.^14^ With 80% power, a 0.05 two-sided significance level, accounting for 21% attrition, and a mean difference in change in CAIDE of 0.186, the required sample size is estimated to be 2319 participants. To allow for unexpected factors, we raised this to 2400.

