Participants have only access to one of two versions of the participant app. Participants randomised to the intervention condition will have access to an interactive smartphone application in their own language (English in the UK and Mandarin in China). The intervention app facilitates coach-supported self-management of seven dementia risk factors, including overweight, unhealthy diet, insufficient physical activity, smoking, hypertension, dyslipidaemia and diabetes. Participants can set personal goals for lifestyle change, following the specific, measurable, achievable, realistic and time-bound principle. Participants receive automated reminders to enter measurements (eg, number of steps and blood pressure) for these goals, facilitating progress monitoring. The intervention participants will receive support from an experienced lifestyle coach, who is trained in motivational interviewing and works according to a coach protocol based on current guidelines for risk factor management. Regular training sessions in each country will enhance uniformity in coaching procedures, taking cultural differences into account. During the baseline visit, after randomisation, the coach discusses the participant’s dementia risk profile, and a first lifestyle goal will be set through the app. After the baseline visit, all communication between the participant and coach will take place through the messaging functionality. Through the coach portal, the coach can view goals and measurements, send tailored education modules, and offer remote support to facilitate sustainable behaviour change.

Participants randomised to the control condition will have access to the control app, which is similar in appearance but only contains education material, lacking interactive features and coach-support. During the baseline visit, control participants will receive concise feedback on their risk profile.

The PRODEMOS intervention in its current design is positioned as add-on to existing care.

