### Randomisation and blinding

After completion of the baseline assessments, participants will be individually randomised in a 1:1 ratio, stratified by country, using a central, computer-generated sequence. Participating cohabiting partners will be allocated to the same study condition. Complete blinding of participants is not possible, owing to the nature of the intervention. Participants will be informed that they will be randomised to one of two lifestyle apps, without further details. All outcome assessments will be done by an independent assessor unaware of treatment allocation.

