#### Data analysis

The effect on the CAIDE Score will be analysed using linear mixed-effect models according to the intention-to-treat principle, taking clustering within partner pairs and country into account by testing best fit for random intercept and/or slope. If needed, we will adjust for baseline imbalances and take clustering of the intervention within centre and/or coach into account. No imputation of the CAIDE Score will be done for the primary analysis. In sensitivity analyses, we will use multiple imputation to assess the impact of missing items needed to calculate the CAIDE Score, provided there are no indications that the variables are missing not at random, and a per-protocol analysis for those adherent to the intervention will be performed. Moreover, we will explore the interaction of intervention duration with the effect of the invention by adding an interaction term (intervention duration*randomisation group) to the main model. This will give insight into the potential additional intervention effect in participants with a follow-up time of less than 18 months.

Subgroup analyses will be performed for country, sex, age group, having a history of CVD, number of risk factors, willingness to change lifestyle (assessed with one question during the baseline visit), participation with(out) a participating partner, having the same coach during the full length of the study and the number of goals set. For all these factors, interaction terms will be included to test for between-subgroup differences in intervention effects.

The effect on individual modifiable components of the CAIDE Score and 10-year CVD Risk Scores will be analysed using linear mixed-effect models according to the intention-to-treat principle, taking clustering within partner pairs and country into account. Self-assessment scales, which are mostly ordinal, will be regarded as linear scales if there are at least four categories and the ‘distance’ between the categories can be regarded equal. Poisson regression or zero-inflated models may be applied to distributions resembling count or zero-inflated data. The choice of the final model will be a compromise between optimal fit and interpretability of the results for a general clinical public.

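### The sample size treats participants as independent although coaching is delivered in the intervention arm only, and the primary model includes coach only conditionally, so power is stated without a known source of clustering

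*Protocol article*

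**What the plan says.** All places are in the protocol article.

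- **Sample size.** The inputs are "With 80% power, a 0.05 two-sided significance level", a target difference of 0.186 CAIDE points, change-score SDs from an earlier trial ("intervention group=−0.290±1.47 SD and control group=−0.104±1.36 SD") and that trial's 21% attrition. The result is given as "accounting for 21% attrition, and a mean difference in change in CAIDE of 0.186, the required sample size is estimated to be 2319 participants". It is raised to 2400 as a reserve for unforeseen factors. No ICC, design effect, couple share or coach caseload appears.
- **Intervention and control condition.** "The intervention participants will receive support from an experienced lifestyle coach". The control app has no coach support.
- **Randomisation and blinding.** "Participating cohabiting partners will be allocated to the same study condition".
- **Data analysis.** The primary mixed model accounts for partner pairs and country. Coach and centre are treated differently: "If needed, we will adjust for baseline imbalances and take clustering of the intervention within centre and/or coach into account". The article gives no criterion for need.
- **Study logistics and data collection.** The health coach conducts the baseline visit, at which participants of both arms are randomised.

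**The concern.** When one coach supports many participants, their outcomes can share that coach's skill or style. Here this applies during follow-up to one arm only, so the design is partially nested. The variance of the intervention mean then has a between-coach part that shrinks with the number of coaches and not with the number of participants.

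Two things follow:

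- The 80% power is derived as if this part were zero, although the article names coach clustering as a possibility. The only margin, 81 people, is reserved for the unforeseen.
- Whether coach enters the primary model is left to a judgement made on the data. If coaches differ and the term is left out, the standard error is too small and the test of the primary effectiveness outcome rejects too often.

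**Working it through.** **1. Reproducing the plan's figure.** Inputs are from the Sample size section: difference 0.186, SDs 1.47 and 1.36, two-sided 5%, 80% power, 21% attrition.

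- Normal approximation: n per arm = 7.849 × (1.47² + 1.36²) / 0.186² = 7.849 × 4.0105 / 0.034596 ≈ 910. Total 1820, and 1820 / 0.79 = 2304.
- With a common SD rounded to 1.42 and the t distribution: 916 per arm, total 1832, and 1832 / 0.79 = 2319.

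The second line matches exactly, with no design effect anywhere in it.

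**2. Power at 2400 without clustering.** Completers per arm = 2400 × 0.79 / 2 = 948. SE = √(4.0105 / 948) = 0.0650. Power = Φ(0.186 / 0.0650 − 1.96) = 81.6%. The increase absorbs an overall design effect of about 1.04 (2400 / 2319 = 1.035; 2400 / 2304 = 1.042).

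**3. Couples.** Design effect = 1 + (share in pairs × ICC). Assuming 30% in pairs and a within-couple ICC of 0.2, this is 1.06 and power at 2400 is 79.3%. At 20% and 0.2 it is 1.04 and power is 80.1%.

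**4. Coach.** The number of coaches J and the coach ICC are assumptions, because the documents give neither. With m = 948 / J completers per coach:

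- intervention-arm design effect DE = 1 + (m − 1) × ICC
- variance of the difference = (1.47² × DE + 1.36²) / 948
- variance inflation V = (1.47² × DE + 1.36²) / 4.0105
- type I error if coach is never modelled = 2 × [1 − Φ(1.96 / √V)]

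Example, J = 10 and ICC = 0.005: m = 94.8, DE = 1 + 93.8 × 0.005 = 1.469, V = (2.1609 × 1.469 + 1.8496) / 4.0105 = 1.253. SE = 0.0728, power = Φ(2.555 − 1.96) = 72.4%. Type I error if coach is ignored = 2 × [1 − Φ(1.751)] = 8.0%.

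| Coaches | ICC 0.001: power | ICC 0.005: power | ICC 0.005: type I, coach ignored | ICC 0.01: power | ICC 0.01: type I, coach ignored |
|---|---|---|---|---|---|
| 10 | 79.7% | 72.4% | 8.0% | 64.5% | 11.0% |
| 20 | 80.6% | 76.9% | 6.5% | 72.5% | 8.0% |
| 30 | 81.0% | 78.5% | 6.0% | 75.5% | 6.9% |
| 40 | 81.1% | 79.3% | 5.7% | 77.0% | 6.4% |

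**5. If need is decided by a test.** One possible reading of the conditional wording is a 5% F test of between-coach variance. With 948 completers, its power is 24%, 18%, 15% and 13% at ICC 0.005 for 10, 20, 30 and 40 coaches, and 47%, 37%, 30% and 26% at ICC 0.01. The whole procedure was simulated under a zero average effect: fit the partially nested analysis if the test is significant, otherwise ignore coach. Its type I error was 5.3–6.3% at ICC 0.005 and 5.6–6.8% at ICC 0.01. Including coach always, with Satterthwaite degrees of freedom, gave 4.9–5.1%.

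**The case against.** **Much larger distortions do not follow.** With 10 coaches and an ICC of 0.03, the same formulas give 44% power and a 22% type I error if coach is ignored, and a reader might take these as the plan's properties. The documents do not support that. The plan does not say coach will never be modelled, and at ICC 0.03 the F test would find the coach variance 89% of the time with 10 coaches and 83% with 30. An ICC of 0.03 also implies a between-coach SD of 1.47 × √0.03 = 0.255 points, more than the whole 0.186 target. This stands, so the conclusion is confined to ICCs of 0.01 or less.

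**Couples are handled.** A reader might infer that the primary test also ignores couples. It does not: partner pairs are in the primary model, and the increase to 2400 absorbs most of their cost. The analysis concern is coach and centre only.

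**The arithmetic is not wrong.** 2319 is correct for the assumptions used. The issue is the assumption of independence.

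**The full analysis plan is elsewhere.** The article says it is published with the registration, and it is not shown here. It may fix when coach is included, so the missing criterion cannot be held against the trial as a whole. It would not alter the power derivation printed in the article.

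**Inflation needs coaches that differ.** If coaching changes nothing for anyone, no coach-delivered variance exists to ignore. The type I figures refer to coaches whose effects vary around a zero average.

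**A coach effect in one arm is a simplification.** Coaches also see controls at the baseline visit, and a planned subgroup on keeping the same coach throughout shows that coaches may change. This stands and shapes the fix.

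**Conclusion.** The point holds in a limited form. The sample size contains no allowance for a form of clustering that the article itself names, and the stated 80% power therefore assumes independent participants. At 2400, power stays near 80% if the coach ICC is about 0.001. It falls to 72–79% at 0.005 and 65–77% at 0.01 with 10 to 40 coaches. The conditional coach term exposes the primary test to a modest excess of false positives: about 5–7% under a test-then-include rule, and up to 8% (ICC 0.005) or 11% (ICC 0.01) only if coach is left out altogether.

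These sizes rest on assumed coach numbers and ICCs, equal caseloads, coach effects in the intervention arm only, and the article's SDs and attrition. They show a range and are not a forecast. The point is worth correcting because the correction is cheap, but it does not invalidate the design.

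**What to change.** 1. **Data analysis section.** Replace the conditional coach wording with a coach random effect that is always in the primary model. Define it by the first assigned coach, let it act in the intervention arm (partially nested), keep the couple intercept alongside it, and use small-sample degrees of freedom. Add a sensitivity analysis in which coach acts in both arms, because the coach also conducts the controls' baseline visit. If the full analysis plan already fixes a rule, bring the two texts into line.
2. **Sample size section.** State the assumed number of coaches, coach ICC and couple share, and give the power that 2400 provides across that range.

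The cost is a change of wording, somewhat wider confidence intervals and a less favourable stated power. No additional enrolment is called for.

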#### Data analysis

The effect on the CAIDE Score will be analysed using linear mixed-effect models according to the intention-to-treat principle, taking clustering within partner pairs and country into account by testing best fit for random intercept and/or slope. If needed, we will adjust for baseline imbalances and take clustering of the intervention within centre and/or coach into account. No imputation of the CAIDE Score will be done for the primary analysis. In sensitivity analyses, we will use multiple imputation to assess the impact of missing items needed to calculate the CAIDE Score, provided there are no indications that the variables are missing not at random, and a per-protocol analysis for those adherent to the intervention will be performed. Moreover, we will explore the interaction of intervention duration with the effect of the invention by adding an interaction term (intervention duration*randomisation group) to the main model. This will give insight into the potential additional intervention effect in participants with a follow-up time of less than 18 months.

Subgroup analyses will be performed for country, sex, age group, having a history of CVD, number of risk factors, willingness to change lifestyle (assessed with one question during the baseline visit), participation with(out) a participating partner, having the same coach during the full length of the study and the number of goals set. For all these factors, interaction terms will be included to test for between-subgroup differences in intervention effects.

The effect on individual modifiable components of the CAIDE Score and 10-year CVD Risk Scores will be analysed using linear mixed-effect models according to the intention-to-treat principle, taking clustering within partner pairs and country into account. Self-assessment scales, which are mostly ordinal, will be regarded as linear scales if there are at least four categories and the ‘distance’ between the categories can be regarded equal. Poisson regression or zero-inflated models may be applied to distributions resembling count or zero-inflated data. The choice of the final model will be a compromise between optimal fit and interpretability of the results for a general clinical public.

Prevalence ratios will be used for self-assessment instruments with defined cut-offs for the presence or absence of a condition, for example, ‘depressive symptoms’ for a GDS >5. For (clinical) dichotomous outcomes, such as incident CVD, dementia or mortality, Cox proportional hazard models will be used with time using baseline as timescale. A sensitivity analysis will be performed using age as timescale.

The full analysis plan, including the health economic analysis plan entailing the cost–consequence analysis of the within-trial results, the cost-effectiveness analyses and the cost–utility analysis and hypotheses for the subgroup analyses, is published on the ISRCTN website: http://www.isrctn.com/ISRCTN15986016.

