**Methods and analysis:**

The prevention of dementia using mobile phone applications (PRODEMOS) randomised controlled trial will follow an effectiveness–implementation hybrid design, taking place in the UK and China. People are eligible if they are 55–75 years old, of low socioeconomic status (UK) or from the general population (China); have ≥2 dementia risk factors; and own a smartphone. 2400 participants will be randomised to either a coach-supported, interactive mHealth platform, facilitating self-management of dementia risk factors, or a static control platform. The intervention and follow-up period will be 18 months. The primary effectiveness outcome is change in the previously validated Cardiovascular Risk Factors, Ageing and Incidence of Dementia dementia risk score. The main secondary outcomes include improvement of individual risk factors and cost-effectiveness. Implementation outcomes include acceptability, adoption, feasibility and sustainability of the intervention.

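### The primary model treats the two-level stratification factor country as a clustering level and settles its random effects by best fit, so the primary test is not fixed in advance and power can be lost

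*Protocol article*

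**What the plan says.** The Data analysis section of the Protocol article describes the primary analysis as an intention-to-treat linear mixed model, "taking clustering within partner pairs and country into account by testing best fit for random intercept and/or slope". The next sentence leaves further terms conditional: "If needed, we will adjust for baseline imbalances and take clustering of the intervention within centre and/or coach into account".

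The abstract describes the trial as "taking place in the UK and China", so country has two levels. Under Randomisation and blinding, "participants will be individually randomised in a 1:1 ratio, stratified by country"; no other stratification factor is stated. The same section explains the clustering by couple: "Participating cohabiting partners will be allocated to the same study condition".

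Data analysis also lists country among the subgroup factors and adds: "For all these factors, interaction terms will be included to test for between-subgroup differences in intervention effects". The sample size rests on "a mean difference in change in CAIDE of 0.186", with no between-country variance component.

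**The concern.** Partner pairs and country are handled alike, as levels over which random effects may be fitted. Pairs are many, and their shared allocation justifies a random intercept. Countries are two, and a variance estimated from two units has one degree of freedom. Such an estimate is close to a restatement of the observed gap between the countries.

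The random structure is then to be decided by how well it fits the trial's own outcome, with no criterion or fallback stated. If a treatment slope by country is among the candidates, the choice changes the standard error of the primary effect, and so can change the conclusion. At stake are the planned 80% power and having one pre-specified primary test.

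**Working it through.** **Inputs.** From Sample size: target difference 0.186; SDs of change 1.47 and 1.36 ("intervention group=−0.290±1.47 SD and control group=−0.104±1.36 SD"); 80% power; two-sided 0.05; 21% attrition; required N 2,319, raised to 2,400. Assumed, because the article does not give them: an equal country split, slope meaning a treatment slope by country, a normal reference distribution, and no partner-pair correlation.

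**1. The plan's own figure.** Pooled SD = √((1.47² + 1.36²)/2) = 1.416. Per arm: 2 × (1.960 + 0.842)² × 1.416² / 0.186² ≈ 910, so 1,820 in total. Dividing by 0.79 gives 2,304, within 1% of 2,319 (an SD rounded to 1.42 gives 2,317). The stated N is thus a plain two-mean comparison.

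**2. Country as a fixed effect.** Completers: 2,400 × 0.79 = 1,896, or 474 per arm per country. SE of each country's effect: s = 1.416 × √(2/474) = 0.0920. SE of the common effect: 0.0920/√2 = 0.0650. Power = Φ(0.186/0.0650 − 1.960) = 81.6%.

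**3. Random country intercept only.** In two fitted examples the SE equalled the fixed-country SE (0.0644 in both models, and 0.0664 in both). There is no inflation.

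**4. Random treatment slope by country.** Let D be the difference between the two observed country effects. REML gives τ² = max(0, D²/2 − s²), and the SE of the mean effect is √((s² + τ²)/2). Whenever τ² > 0 this reduces to |D|/2: the standard error is half the gap between the countries, whatever the sample size.

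**5. Same data, two criteria.** Take observed effects 0.331 and 0.041 (mean 0.186, D = 0.290).
- Slope kept: SE = 0.290/2 = 0.145, z = 1.28, p = 0.20.
- Slope dropped: SE = 0.0650, z = 2.86, p = 0.004.
- Fit statistic: x = D²/(2s²) = 0.04205/0.00846 = 4.97, and the REML likelihood-ratio statistic is x − 1 − ln x = 2.37.
- AIC, with one extra parameter, keeps the slope above 2. The 5% boundary likelihood-ratio test keeps it above 2.71. The two disagree here.

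Solving x − 1 − ln x = 2 and = 2.71 gives x = 4.51 and 5.39. With D = s√(2x), the two criteria disagree for observed gaps of about 0.276 to 0.302.

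**6. Power under selection.** The two country effects were simulated as normal with SE s, the slope was kept or dropped by each criterion, and the mean effect was tested at 1.96.

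| True effects | Country fixed | AIC-selected | LRT-selected |
|---|---|---|---|
| 0.186, 0.186 | 82% | 79% | 80% |
| 0.25, 0.122 | 82% | 72% | 74% |
| 0.286, 0.086 | 82% | 59% | 64% |

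With equal true effects the slope is kept in 3.4% of trials by AIC and 2.0% by the likelihood-ratio test. A 70:30 country split gives nearly the same result for equal effects (81.7% fixed; 79.1% and 80.1% selected).

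**7. Type I error.** With zero effect in both countries, rejection is 5.0% with country fixed and about 4.9% under either selection rule.

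**The case against.** The strongest reply is that the rule is a selection rule, and that under the design assumption of one common effect it rarely selects the harmful structure. That stands: the average loss is then only 2 to 3 points. Larger losses need real differences between countries, and the article gives no country-specific effects or country split.

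Slope is also undefined. If it means a slope over time, the standard-error argument weakens, and only the choice by fit remains. The wording also permits an intercept alone, which is harmless to the SE.

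The article says that the full analysis plan is published separately. It is not shown here and may define the slope, the criterion and the model. The complaint is nevertheless about a rule that the article states, not about missing detail.

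A reader might infer four stronger things that the article does not support:
- That power falls to 71%, 59% or 43% in the three scenarios above. Those are the figures if a random country slope is always fitted, and the article does not say that it will be.
- That the trial could not reject at all. This needs a t reference with one degree of freedom, and the article names no degrees-of-freedom method.
- That the choice is made on unblinded data. The article does not say when or on what data it is made. Testing a treatment slope would need the allocation; choosing an intercept would not.
- That false positives rise. For the structures modelled and a homogeneous null, they do not.

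**Conclusion.** The point holds in limited form and should be fixed. The article treats a two-level stratification factor as a source of random variation and leaves the random structure of its primary test to an unspecified comparison of fit. The harm is lost power and a primary p-value that is not fixed in advance. The loss is 2 to 3 points if the effect is the same in both countries. It is about 8 to 10 points for true effects of 0.25 and 0.122, and about 18 to 23 points for 0.286 and 0.086. These sizes rest on the assumptions listed under Inputs, above all that slope means a treatment slope by country. The random effect for partner pairs is sound in principle and is no part of the fault.

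**What to change.** State one primary model in advance: treatment, country as a fixed effect, and a random intercept for partner pair. For the primary analysis, delete the clause that settles the random structure by fit. Assess differences between countries only through the country-by-group interaction that is already planned. If the separately published analysis plan already fixes the model, reconcile the two texts.

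The change is one of wording; it needs no more participants or data. Its price is that the inference refers to these two countries and not to a wider population of countries. Little is given up, because two countries cannot support the wider inference under either model. If country effects are viewed as draws with mean zero and SD 0.10 (an assumed value, with an equal split), the fixed-country test rejects in 18.5% of simulated trials and an always-fitted random slope still rejects in 11.6%.
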